While the HEART score has been well validated in the ED setting, it has yet to be implemented in a prehospital setting. Paramedics are often the first providers to evaluate and begin treating patients with symptoms concerning for ACS. Current pre-hospital risk stratification is largely based on a combination of ECG results and paramedic gestalt. Since ECGs without signs of a STEMI are poor predictors of ACS, paramedics often have difficulty distinguishing high-risk patients from low-risk patients. Therefore, integrating objective risk stratification tools, such as the HEART score and point-of-care troponin testing, into Emergency Medical Services (EMS) triage and destination plans represents an opportunity to improve care. Furthermore, expanding use of the HEART score to paramedics in the pre-hospital setting is a natural extension of our prior work, especially given the growing sophistication of mobile integrated healthcare (“community paramedicine”) over the last decade. Thus, **multidisciplinary leaders within Emergency Medicine, Cardiology, and Prehospital Medicine have agreed that a limited/pilot evaluation of the HEART Score with Abbott’s i-STAT^®^ point-of-care (POC) troponin testing in the prehospital setting is needed.**

We anticipate that a standardized approach to paramedic risk stratification using the HEART score with Abbott’s i-STAT^®^ POC troponin testing will be feasible and achieve high accuracy for the detection of ACS. Ultimately we believe this planned implementation will improve the quality and value of chest pain care. Placing these tools in the hands of our first responders will identify patients with ACS earlier and speed the delivery of potentially life-saving care. For example, EMS triage and destination plans (chest pain treatment and transportation triage and destination plans) could be amended so that patients with positive POC troponins or high HEART scores could be transported directly to a hospital with cardiac catheterization capabilities, avoiding delays and costs associated with inter-facility transfers. However, before EMS triage and destination plans can fully incorporate the HEART score and POC troponin testing, first the feasibility of such an implementation must be established by collecting quality surveillance data.

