## A2. Primary Hypotheses

- Paramedics using the HEART score and Abbott’s i-STAT^®^ point-of-care troponin assay in the pre-hospital setting will achieve 98% sensitivity and negative predictive value for MACE during the index visit and at 30 days in patients with symptoms concerning for ACS.
- Inter-rater reliability (kappa) for HEART scores calculated by ED physicians in a hospital setting and paramedics in the pre-hospital setting using Abbott’s i-STAT^®^ point-of-care troponin assay will exceed 0.60.

##

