## A3. Purpose of the Project Protocol

The objective of this pilot project is to establish the feasibility and accuracy of prehospital HEART score assessment using an Abbott’s i-STAT^®^ point-of-care troponin assay. If feasibility and accuracy can be established, the HEART score and POC troponin testing will allow modification of triage and destination plans so that patients can be transported to the most appropriate hospital settings as part of a larger implementation evaluation and to speed the delivery of ACS care. For example, patients with positive troponins and high HEART scores could be triaged to facilities with on-site cardiac catheterization laboratories, avoiding costly and inefficient inter-facility transfers. Furthermore, early risk stratification with the HEART Score, is likely to result in downstream efficiency gains; decreasing the ED length of stay for patients with low-risk chest pain.

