## C. Primary Aims

- **Specific Aim 1:** Perform validation (quality control) of the Abbott i-STAT^®^ point-of-care troponin assay in an ambulance; comparing troponin measurements from patient’s blood samples analyzed in a moving ambulance vs a laboratory setting.
- **Specific Aim 2**: Determine whether paramedics using the HEART score and Abbott’s i-STAT^®^ point-of-care troponin assay in the pre-hospital setting can achieve 98% sensitivity and negative predictive value for major adverse cardiac events (MACE: cardiac death, myocardial infarction, or coronary revascularization) during the index visit and at 30 days in patients with symptoms concerning for ACS.
- **Specific Aim 3:** Test whether the inter-rater reliability (kappa) for risk assessment using the HEART score and Abbott’s i-STAT^®^ point-of-care troponin assay between ED physicians and paramedics exceeds 0.60.
- **Specific Aim 4:** Determine the potential impact of prehospital HEART Score and Abbott i-STAT^®^ point-of-care troponin measurement on the following efficiency outcomes: ED length of stay (LOS), hospitalization rate, and rate of objective cardiac testing (stress testing and coronary angiography).
- **Specific Aim 5**: Determine whether pre-hospital Abbott i-STAT^®^ point-of-care troponins are independent predictors of MACE during index hospitalization and at 30 days in patients with symptoms concerning for ACS.

Rationale for the Selection of Outcome Measures

In order for a chest pain risk stratification tool to be considered effective and achieve widespread adoption in the prehospital setting it must accurately detect patients with MACE and there must be high agreement between the paramedics and ED providers. While the HEART Score and troponin testing are well validated for risk stratification in the ED setting, feasibility and accuracy in the prehospital setting have yet to be tested as part of a clinical implementation. Furthermore, the inter-rater reliability (kappa) between paramedics and ED providers has not been tested.

Rationale for 30 day follow-up period

MACE outcomes will be assessed from the index visit through 30 days. ED ACS risk stratification evaluations have traditionally focused on 30 day end-points as recommended in the standardized reporting guidelines for ACS.[^19^](#_ENREF_19)

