**F. Statistical Plan**

F1. Overview

The primary concept of the PARA-HEART project is to evaluate whether paramedics can be taught to calculate a HEART score accurately with acceptable intra-observer reliability (when compared to ED physician assessments). This project is a clinical pilot study in order to generate data to support a larger and non-observational implementation. If we are able to show that these scores can be reliably predict MACE and agree with ED physicians assessments, then we can start using the HEART score in the pre-hospital setting to alter care and transport triage and destination plans.

F2. Sample Size and Power

The PARA-HEART project is a clinical pilot study in which we hope to demonstrate that paramedics are able to achieve 98% sensitivity for the detection of MACE. To achieve a sensitivity of 98% with a lower bound of the 95% confidence interval that exceeds 90% we will need at least 50 patients with MACE events. Assuming a 10% MACE rate among our chest pain population,[^4-7^](#_ENREF_4) to include 50 patients with adverse events we will need a total sample size of 500 patients.

F3. Analysis Plan and Statistical Methods

The percentage of patients identified by paramedics using the HEART Score with POC troponin testing as high- and low-risk, the sensitivity, specificity, and positive and negative predictive values, positive and negative likelihood ratios, and accuracy for MACE will be calculated. Corresponding 95% exact binomial confidence intervals will be computed.

The proportion of patients receiving objective cardiac stress testing, cardiac catheterization, myocardial infarction, or cardiac death during the index hospitalization will be estimated for subjects classified as high and low risk by ED physicians and compared with those classified as high and low risk by paramedic assessment. Cardiac-related ED visits and readmission to the hospital will be calculated at 30 day follow-up. LOS will be reported using descriptive statistics, including median and inter-quartile range as this outcome tends to have a nonparametric distribution.

HEART scores calculated by the blinded primary ED provider will be compared to the HEART scores obtained by the paramedics. Raw percent agreement and kappa scores will be determined to assess intra-observer reliability. A kappa of >0.75 will be defined as excellent agreement, 0.60-0.74 will be defined as acceptable agreement, and <0.59 will be defined as unacceptable agreement.

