*Post-Hoc Analysis of Troponin Cut Points:* For the clinical pilot, paramedics will use a cut point of 0.08 ng/mL, which corresponds to the published 99^th^ percentile upper reference limit for the assay. However, following completion of the pilot we will analyze different troponin cut points (including 0.04 ng/mL) used alone or in combination with the HEART score to find the combination with the greatest accuracy (area under the curve in a receiver operator curve).

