***Analytical and Functional Sensitivities***

- *The analytical sensitivity of the cTnI method is 0.02 ng/mL, which is the lowest cTnI level that can be distinguished from zero. The analytical sensitivity is defined as the concentration at two standard deviations from a sample at 0.00 ng/mL.*
- *Another characteristic of an analytical measurement is the functional sensitivity, which is defined as the cTnI level at which the test method displays a particular percent coefficient of variation (%CV). Estimates of the 20% and 10% functional sensitivity for the cTnI method were determined from whole blood measurements. The 20% and 10% functional sensitivities for the cTnI method are 0.07 ng/mL and 0.10 ng/mL, respectively*

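### The troponin cut-point search ranks candidates by ROC area, a criterion that does not protect sensitivity and so does not match the trial's own target of 98% sensitivity and NPV

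*Protocol*

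**What the plan says.** Section F3 of the protocol (Post-Hoc Analysis of Troponin Cut Points) fixes 0.08 ng/mL as the cut point during the pilot. Afterwards other cut points, with 0.04 ng/mL named, will be examined on their own or together with the HEART score "to find the combination with the greatest accuracy (area under the curve in a receiver operator curve"). No minimum sensitivity or NPV is attached to that choice.

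Elsewhere the protocol judges the tool by missed events:

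- Section A2: paramedic assessment "will achieve 98% sensitivity and negative predictive value for MACE during the index visit and at 30 days".
- Section C (Aim 2) asks whether paramedics "can achieve 98% sensitivity and negative predictive value for major adverse cardiac events".
- Section F2 sizes the study on sensitivity alone: to reach 98% "with a lower bound of the 95% confidence interval that exceeds 90% we will need at least 50 patients with MACE events". It continues: "Assuming a 10% MACE rate among our chest pain population", hence 500 patients.
- Section E2 defines a missed MACE as one in a patient rated low risk.

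**The concern.** The primary question and the cut-point search use different yardsticks. The primary question asks whether nearly all MACE are caught. The search asks which candidate has the largest ROC area, and that quantity can rise while sensitivity falls. Followed as written, F3 can name as best a combination that fails the target by which the pilot itself is judged, and can rank below it one that meets the target.

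At stake is which combination the pilot reports as best. The primary result is not at stake. The criterion is written into the protocol, so this is a stated choice and not a detail left for a statistical analysis plan.

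**Working it through.** **Inputs from the protocol.** Target sensitivity and NPV 98% (A2, C); 50 MACE in 500 patients at a 10% rate (F2); exact binomial 95% intervals (F3). The protocol gives no specificity or ROC area for any candidate, so those values below are assumptions.

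**The plan's own figure.** 50/0.10 = 500 reproduces the sample size. At 49/50 = 98% the exact two-sided 95% lower limit is 89.4%, just short of the 90% in F2; with one miss, the limit first exceeds 90% at 54 events. That is a separate matter, and nothing below depends on it.

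**Step 1: area of a single yes/no rule.** The ROC curve has one interior point, and the area is (Se + Sp)/2. The Mann-Whitney form confirms this: Se 0.80 and Sp 0.80 give 0.80.

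**Step 2: two assumed rules, 50 MACE and 450 non-MACE.**

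| Rule | Area | MACE missed | True negatives | NPV |
|---|---|---|---|---|
| Se 98%, Sp 40% | (0.98 + 0.40)/2 = 0.69 | 50 × 0.02 = 1 | 450 × 0.40 = 180 | 180/181 = 99.4% |
| Se 60%, Sp 95% | (0.60 + 0.95)/2 = 0.775 | 50 × 0.40 = 20 | 450 × 0.95 = 427.5 | 427.5/447.5 = 95.5% |

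The second rule wins on area and fails both targets. Less extreme pairs behave alike. Se 80%, Sp 80% has area 0.80 and also beats the first rule, with 10 of 50 missed and NPV 360/370 = 97.3%.

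**Step 3: a range, so that the point does not rest on one pair.** Take an equal-variance binormal marker with overall AUC A, and set d = √2 × Φ⁻¹(A). The cut that maximises (Se + Sp)/2 has Se = Sp = Φ(d/2). Holding Se at 98% leaves Sp = Φ(Φ⁻¹(0.02) + d). NPV = 0.9 Sp/[0.9 Sp + 0.1(1 − Se)].

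| Assumed AUC | Se = Sp at the area-maximising cut | NPV there | Sp if Se is held at 98% | Binary area at that cut |
|---|---|---|---|---|
| 0.75 | 68% | 95.1% | 14% | 0.56 |
| 0.80 | 72% | 95.9% | 19% | 0.59 |
| 0.85 | 77% | 96.8% | 28% | 0.63 |
| 0.90 | 82% | 97.6% | 40% | 0.69 |

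Across this range the chosen cut misses both 98% targets.

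**Step 4: the other reading.** F3 may mean that the troponin item of the HEART score is re-scored at each cut point and the area is taken over the whole score. The area is then no longer a plain average of one Se and one Sp. Assume three ordered categories (low, middle, high), with non-MACE patients split 40/50/10%:

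- Score A, MACE split 2/58/40%: area = 0.02 × 0.20 + 0.58 × 0.65 + 0.40 × 0.95 = 0.761; sensitivity at the low-risk cut 98%.
- Score B, MACE split 8/27/65%: area = 0.08 × 0.20 + 0.27 × 0.65 + 0.65 × 0.95 = 0.809; sensitivity at the low-risk cut 92%.

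Both have 40% specificity at that cut. B wins on area and is worse where missed MACE is counted.

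**The case against.** The strongest reply is that little hangs on this analysis. F3 labels it post hoc, the primary analysis keeps 0.08 ng/mL, and nothing says that the winner will be adopted or will replace that value. The 98% figure is a hypothesis, and F2 speaks only of hoping to demonstrate it. All of that stands. It limits the importance of the point but does not make the criterion fit the aim.

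Second, equal weighting of sensitivity and specificity is exact only for a dichotomous rule, and F3 does not say which kind of area is meant. That stands too, but Step 4 shows that the full-score reading does not protect sensitivity at the low-risk cut either.

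Third, a hard floor on observed sensitivity is brittle. With 50 events it allows one miss; with 49 it allows none, since 48/49 = 97.96%. With 50 events a rule of true sensitivity 98% would be discarded about 26% of the time (1 − 0.98⁵⁰ − 50 × 0.02 × 0.98⁴⁹), and one of 95% kept about 28% of the time (0.95⁵⁰ + 50 × 0.05 × 0.95⁴⁹). This is a fair warning about the remedy, and the fix allows for it.

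A reader might infer three further faults that the protocol does not support:

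- **No correction for optimism.** The protocol is silent, but a statistical analysis plan could supply this. In simulations under assumed values the effect was modest, about 0.01 to 0.05 in area.
- **Testing 0.04 ng/mL is an error because of assay imprecision.** Attachment K2 itself discloses that "The 20% and 10% functional sensitivities for the cTnI method are 0.07 ng/mL and 0.10 ng/mL, respectively". Exploring a lower value afterwards is not a mistake, and for the same rule a lower cut point cannot reduce sensitivity.
- **Sections A1 and A3 contradict each other on how troponin and HEART combine.** A1 says "patients with positive POC troponins or high HEART scores could be transported directly to a hospital" and A3 says "patients with positive troponins and high HEART scores could be triaged to facilities". Both are examples of possible future triage, not candidate rules for this search.

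**Conclusion.** The point holds in a limited form. The criterion fixed in F3 does not protect sensitivity and does not match the 98% sensitivity and NPV target. Under the assumed values it can prefer a rule missing 20 of 50 MACE to one missing 1. For the assumed binormal markers the area-maximising binary cut has sensitivity of about 68% to 82%. These sizes are illustrations; they rest on the assumed specificities, the equal-variance binormal form and the protocol's 10% MACE rate, and they do not predict what the pilot will find.

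It would go too far to read this as a flaw in the primary analysis, as breach of a binding 98% requirement, or as evidence that an insensitive rule will be put into use. The primary analysis at 0.08 ng/mL is untouched, and the protocol commits to no use of the winning combination. No view is taken here on which clinical cut point is right.

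**What to change.** In F3, replace selection by greatest ROC area with a criterion tied to the trial's target:

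1. List the candidates, including re-scoring the HEART troponin item at each cut point, and say whether each is a yes/no rule or a full score read at the low-risk cut.
2. For each, report sensitivity and NPV with exact 95% intervals.
3. Compare specificity only among candidates compatible with the 98% sensitivity and NPV target, and state beforehand how compatibility is judged. With 50 events, an observed sensitivity of at least 98% allows one miss. Requiring only that the exact 95% interval reach 98% allows three (upper limit 98.7% at 47/50, 97.8% at 46/50).
4. Keep ROC area as a descriptive secondary measure.
5. Describe the result as exploratory.

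The cost is wording and some analysis time, with no new data and no change in care. The downside is imprecision: with about 50 events a single miss can decide whether a candidate passes an observed floor, and possibly none will pass. The intervals must therefore accompany any choice, and a finding that no candidate qualifies should be reported as such.

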## F4. Missing Outcome Data

Based on prior studies we expect >90% to have complete follow-up data from the EMR or phone follow up calls. Participants without follow up data will be searched for the Social Security Death Master File. Those with missing outcome data will be treated as censored and will be considered to have not had a safety event. A planed sensitivity analysis will be used to test this assumption.

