## E. Project Procedures

## E1. Clinical Data Collection

For quality assurance data collection, participants will be identified retrospectively and data will be collected electronically using EHR (EMS records, and WFBH medical records) and via telephone follow-up calls.

Paramedics will use a worksheet to obtain the historical and clinical data needed to calculate a HEART score and this will include recording the POC troponin results. This worksheet will be an investigational record integrated into their normal reporting workflow. Data entered on this worksheet will be abstracted retrospectively. Data obtained will include demographic information (age, gender, race, ethnicity), date and time elements, characteristics of chest pain, ECG interpretation, cardiac risk factors (such as, prior coronary artery disease, smoking, hypertension, diabetes, hyperlipidemia, etc), POC troponin value, and the HEART score.

Since all participants will be transported to WFBMC ED, where the HEART Pathway is part of standard care, we will use the electronic medical record (EMR) to obtain ED physician HEART Score assessments and WFBMC troponin results. These data will be compared to paramedic assessments for determination of inter-observer agreement and correlation. We will also use the EMR to track index outcomes and 30 day events that occur within the WFBH system. Data collected from the WFBH EMR will include patient demographics, history and physical examination data, past medical history, cardiovascular risk factors, ECG results, laboratory results, HEART score and HEART Pathway assessments, ED and discharge diagnoses, disposition, index visit length of stay, objective cardiac testing at the index visit or within 30 days, recurrent ED visits, re-admissions, coronary revascularization, and MI or death within the follow-up period.

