In addition to electronic surveillance, follow up phone calls will be used to determine outcomes at 30 days. EMS or project staff will contact each participant at 30-90 days following their pre-hospital encounter using a modified version of a previously described scripted follow-up dialogue[^23^](#_ENREF_23) to further clarify events since discharge, identify events occurring at other care facilities, and to determine health care utilization since discharge. Events of interest will include MACE (cardiac death, acute myocardial infarction, and coronary revascularization), hospitalizations, and objective cardiac testing (stress testing and coronary angiography), and recurrent ED visits. Participants still unable to be contacted will be considered censored at their last known contact unless record review reveals an event occurred, in which case the patient will be considered to have experienced an event. Participants unable to be contacted will be searched for in the Social Security Death Master File. In the event of discrepancy between a participant’s event reporting and the medical record, the medical record will be considered correct.

*Rationale for phone follow up:*  In order to determine the accuracy of paramedic HEART Score assessments for MACE we will need to have a low lost-to-follow-up rate. Without telephone follow-up calls patients who seek follow-up or recurrent care or have adverse events at non-WFBH facilities will not be detected. Furthermore, it is common practice for EMS agencies to use phone follow up to contact patients for quality assurance purposes. Using the above methods we expect to have a lost to follow-up rate less than 10%.

E2. Outcomes

*2a. Primary Outcome*

The primary outcome is MACE at 30 days. MACE is a composite outcome of cardiac death, acute myocardial infarction, and coronary revascularization. MACE occurring in patients with a low-risk HEART score assessment will be considered missed MACE. The primary outcome will be used to determine the sensitivity, negative predictive value, specificity, positive predictive value, likelihood ratios, and accuracy for paramedic detection of MACE at 30 days using the HEART score with i-STAT POC troponin testing.

The definition of cardiovascular death will be based on the Action to Control Cardiovascular Risk in Diabetes (ACCORD) trial.[^24^](#_ENREF_24) Death from stroke will not be considered a cardiac death.

Modified ACCORD definition of Cardiovascular Death:

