### E3. Detection

MACE will be assessed at 30 days through the EMR and scripted phone follow up calls. Participants without EMR or phone follow up data will be searched for in the Social Security Death Master File.

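### E1 and E3/F4 give different rules for who is lost to follow-up and who is searched in the death file, so a patient never reached by phone can count as complete on the WFBH record alone

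*Protocol*

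**What the plan says.** Three sections of the protocol deal with patients whose 30-day outcome may be unknown.

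- **E1 (Clinical Data Collection).** On status: "Participants still unable to be contacted will be considered censored at their last known contact unless record review reveals an event occurred". On the death search: "Participants unable to be contacted will be searched for in the Social Security Death Master File". The search does not depend on what the record holds. E1 also limits what the record can show: "We will also use the EMR to track index outcomes and 30 day events that occur within the WFBH system". Its reason for phoning is explicit: "Without telephone follow-up calls patients who seek follow-up or recurrent care or have adverse events at non-WFBH facilities will not be detected". E1 expects fewer than 10% to be lost.
- **E3 (Detection).** The first sentence assesses MACE through the EMR together with phone calls. The second sets a narrower trigger for the death search: "Participants without EMR or phone follow up data will be searched for in the Social Security Death Master File".
- **F4 (Missing Outcome Data).** "we expect >90% to have complete follow-up data from the EMR or phone follow up calls", followed by "Participants without follow up data will be searched for the Social Security Death Master File". Patients with missing outcomes are censored and scored as having had no event, and a sensitivity analysis is planned to test that assumption.

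**The concern.** The same patient can be handled in two ways. E1 turns on whether the patient was contacted, and for an unreached patient the record can establish an event but is given no power to establish its absence. E3 and F4 turn on whether any EMR or phone follow-up data exist, so the record alone may be enough to make the patient complete and event-free. E1 explains why that is unsafe: the record sees only WFBH.

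Three things are at stake:

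- **Death ascertainment.** A cardiac death outside WFBH could go unsearched.
- **The reported follow-up rate.** Whether loss stays under 10% depends partly on a term the protocol does not define.
- **The reach of F4's sensitivity analysis.** It can test the no-event assumption only in patients classed as missing. An unreached patient classed as complete is exempt from the test that F4 relies on.

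Sensitivity and NPV for 30-day MACE are the main accuracy results, and F1 says they are meant to support later changes to triage and transport. It should therefore be clear which negatives were verified.

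**Working it through.** **1. The plan's own figures.** F2: events needed / MACE rate = 50 / 0.10 = 500, which reproduces. E1's loss ceiling: 500 × 0.10 = 50 patients.

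**2. One patient under each rule.** Take a patient never reached by phone, with no event in the WFBH record.

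| Question | E1 | E3 and F4 |
|---|---|---|
| Status | Censored at last known contact | Complete if EMR follow-up data exist; otherwise missing |
| Death-file search | Yes | Only if neither EMR nor phone data exist |
| Counted as lost | Yes, unless last known contact covers day 30 | Not if EMR data count |
| In F4's sensitivity analysis | Yes, as censored | Not if EMR data count |
| Score in the main estimate | No event (F4) | No event, complete or missing |

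The first four rows can differ. The last is the same on both sides.

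**3. How many patients.** Phone reach is not given. Assume 5-30% are not reached: 500 × 0.05 = 25 to 500 × 0.30 = 150. This is the ceiling on the patients affected. How many of them change class depends on what counts as EMR follow-up data:

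- If only an entry that covers day 30 counts, few or none are wrongly classed as complete.
- If any WFBH record counts, all are, because every participant is taken to WFBMC ED and has one.

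The protocol does not place itself between these two.

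**4. Outside events among them.** Assume 0.5-4% have an event that the WFBH record cannot show. Then 25 × 0.005 = 0.1 to 150 × 0.04 = 6 events. This covers all MACE in all unreached patients, at either risk level. The death file can reveal only deaths, and a death must be judged cardiac before it counts as MACE.

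**5. Effect on the main estimate.** F4 scores missing patients as event-free, so moving a patient from complete to missing changes nothing in the main estimate. Only a cardiac death found by the wider search does. Starting from 49 of 50 detected:

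| Cardiac deaths found in low-risk patients | Sensitivity | Exact 95% lower limit |
|---|---|---|
| 0 | 49/50 = 98.0% | 89.4% |
| 1 | 49/51 = 96.1% | 86.5% |
| 2 | 49/52 = 94.2% | 84.1% |

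A death found in a high-risk patient would leave sensitivity where it was (50/51 = 98.0%). That 49/50 already falls short of F2's 90% bound under exact limits is a separate matter.

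**6. NPV.** The low-risk share is not given. At an assumed 40-50% (200-250 patients), three false negatives in all give 197/200 = 98.5% to 247/250 = 98.8%, still above 98%. NPV is much less exposed than sensitivity.

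**The case against.** The strongest reply is that the protocol never says an index record is follow-up. E1 separates index outcomes from 30-day events, and the data descriptions in J1 list the index visit and the follow-up period separately. If index records counted, completeness would be close to 100%, and F4's figure of over 90%, its death search and its sensitivity analysis would have no purpose. This stands. A reader might infer that nearly all 500 patients become complete on arrival, that loss under 10% is achieved by definition and that the sensitivity analysis is empty. The documents do not support this; they support a group narrowed by an undefined amount.

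It can also be said that E1's loss figure rests on record and phone together, so it is compatible with F4's; that E1's last known contact need not be a phone contact; and that E3's first sentence joins the two sources. These points soften the conflict over who is lost. They do not remove the conflict over who is searched: E1 searches everyone not contacted, while E3 and F4 search only those lacking both sources.

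E4 mentions claims data when available, and J5 mentions insurers, so WFBH may not be the only source besides the phone. Coverage is not stated, and E3 does not list claims as a means of detection.

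Finally, an operational definition of complete follow-up could sit in the SAP or in the manual of procedures (G3). That is fair for the detail. It does not excuse three protocol sections that give different instructions.

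**Conclusion.** The inconsistency is real and should be corrected. E1 conflicts with E3 and F4 on the death search, and E3 and F4 allow an unreached patient to be classed as complete on a record that, by E1's own account, cannot exclude an event elsewhere. The consequences are a possibly missed death search, an understated loss to follow-up and a sensitivity analysis that leaves out some of the patients it is meant to cover. The number affected cannot be derived from the protocol; 25-150 is a ceiling that rests on an assumed 5-30% not reached.

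A reader might also infer that reclassifying these patients would by itself lower sensitivity from 98.0% to 96.1% or 94.2%. It would not. Those figures apply only if the wider search finds one or two cardiac deaths in low-risk patients. Outside infarctions and revascularizations stay hidden in the main estimate under either rule, because F4 scores missing outcomes as no event.

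**What to change.** Use one rule in E1, E3 and F4:

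1. Run the death-file search for everyone not reached by phone, as E1 already states.
2. Count the 30-day outcome as known only if the patient or a proxy was contacted at or after day 30, or a record entry at or after day 30 documents status over the interval, or a MACE or death by day 30 is documented.
3. Count everyone else as lost, include them in the reported loss-to-follow-up rate, and put them in F4's sensitivity analysis.

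Replace the wording in E3 and F4 that accepts either source with a reference to this rule. Finer operational detail can go to the SAP or the manual of procedures.

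The cost is wording in three sections, one variable derived from data already collected, and a larger death-file search. The sample size stays at 500. The reported loss to follow-up may exceed 10%.
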